### Study treatments

Screening is performed during the routine clinical tinnitus-consultations, and no additional study specific investigations are necessary to determine eligibility. After screening, written informed consent, baseline assessments, and randomization, patients will be treated with either real or sham low-frequency rTMS over a period of 2 weeks. rTMS will be administered according to current safety guidelines [24]. Magstim Super Rapid (The Magstim Company Ltd, Whitland, UK) or Medtronic MagPro (Medtronic GmbH & Co. KG, Düsseldorf, Germany) stimulators will be used for stimulation as available in the participating centers. Figure-of-eight-coils will be used for real stimulation. Sham stimulation will be carried out by tilting the coil 45° away from the skull with one wing touching the skull. The stimulation parameters have been chosen according to successful pilot studies [15,25] and modified with respect to duration, coil positioning and control condition. Recent data point to a dose-response relationship of rTMS treatment in a variety of neuropsychiatric diseases as well as in tinnitus treatment [23,26]. Furthermore, coil positioning using the 10–20 EEG-system has been proven to guarantee exact placement of the TMS coil over the auditory cortex without the need of using MR- and PET-guidance. Finally, finding an adequate placebo condition [27] is still under debate in clinical rTMS studies [28]. Here, sham stimulation will be performed by distortion of the magnetic coil 45° away from the skull with one wing touching the skull. In contrast to sham coils, this kind of sham stimulation does not induce a sufficiently strong magnetic field in the brain tissue to evoke any biological response but is still eliciting some kind of skull sensation. Especially in the context of tinnitus treatment studies, controlling for somatosensory stimulation seems to be critical since somatosensory input is able to modulate tinnitus sensation [1].

After screening, written informed consent, and baseline assessments, patients will be randomized to one of two parallel groups with the following stimulation parameters:

**Treatment group **will receive real stimulation: 2 × 5 sessions, 1 Hz rTMS, stimulation intensity 110% related to the individual resting motor threshold, 2000 stimuli per session, coil position 10–20 guided over left primary auditory cortex.

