#### Secondary objectives

To evaluate the efficacy of real rTMS versus sham rTMS

- in reducing tinnitus severity according to the tinnitus questionnaire of Goebel & Hiller and Tinnitus Handicap Inventory (THI; a self-rating questionnaire; [31]) during the follow-up period (screening versus baseline versus days 5, 12, 18, and weeks 10 and 26),

- in changes of quality of life of patients as measured by the SF 12 (a self-rating questionnaire [32]; baseline versus days 5, 12, 18, and weeks 10 and 26),

- in changes of depressive symptoms as measured by the Beck Depression Inventory (BDI; a self-rating questionnaire; [33]; baseline versus days 5, 12, 18, and weeks 10 and 26),

- in changes of psychometric parameters of tinnitus (tinnitus minimal masking level and tinnitus loudness) as assessed by audiological evaluation (screening versus day 18),

- in changes of structural and functional neuroplastic adaption processes as detected by voxel-based morphometry (VBM) and paired-pulse TMS (baseline versus day 12).

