### Randomization

Before the trial starts, randomization lists will be generated by the Clinical Trials Center, University Medical Center Freiburg, with a 1:1 treatment ratio, stratified by study center and with randomly varying block sizes. At each center, local investigators will have to confirm eligibility of enrolled patients and the non-blinded study staff will forward their request for randomization by fax to the randomization center, located at the department of the lead investigator. There, the randomization lists will be securely stored with none of the clinical staff involved in the trial having access to it. The randomization center will send the allocated treatment by fax to the local non-blinded staff performing rTMS. In addition, a standard email including a statement that the patient has been successfully randomized, will be send to both, the blinded and non-blinded study staff of the center as well as to the monitor.

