### Statistical Analysis

The primary endpoint for evaluation of efficacy of rTMS for tinnitus is the change from baseline to day 12 in the tinnitus score (TQ total score). The treatment effect will be estimated on an intention-to-treat basis including all patients with post-baseline data (carrying forward day 5 measurements if day 12 is missing), in an analysis of covariance including treatment and average baseline score as fixed factors and center as a random factor. Interim analysis for TQ change at day 12 will be carried out on the first 76 randomized patients following an O'Brien and Fleming type sequential design with overall two-sided significance level 0.05 (0.0052 at interim, 0.0481 at final analysis; [38]). If more than 5% of patients fail to provide post-baseline data, the primary analysis will be complemented by sensitivity analyses exploring potential biases induced by patterns of missingness which will be investigated by logistic regression on comprehensive baseline information.

Secondary analyses of TQ change over time will be performed in longitudinal linear mixed models based with a pre-specified model-building strategy. For the other secondary objectives with respect to rating scales (THI, SF 12, BDI, and CGI) a similar strategy will be employed as applicable. For changes in cortical excitability and changes in psychometric parameters of tinnitus assessed by audiological examination, one-way ANOVA analysis will be used, and for changes in brain structure voxel-based morphometry (VBM) will be used.

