### Timing

The start of the study is February 2008. With a planned number of 138 patients providing post-baseline data, a drop out rate for the primary outcome of less than 5% and an expected screening to inclusion ratio of 5:1, 750 patients will have to be assessed for eligibility in all 8 centers, and 150 will be allocated for trial participation. The recruitment and treatment period will be 27 months, with 6 additional months to complete follow-up. Analyses and reporting will be estimated to be 6 months, resulting in a total duration of about 3 years.

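### One-way ANOVA of change for the audiological and cortical-excitability outcomes gives up precision that the primary analysis's ANCOVA form would recover from data already collected

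*Protocol article*

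**What the plan says.** The Statistical Analysis section of the protocol article assigns a method to each group of outcomes. For two of the secondary groups it states: "For changes in cortical excitability and changes in psychometric parameters of tinnitus assessed by audiological examination, one-way ANOVA analysis will be used". The Secondary objectives section defines these changes. For audiology the objective is "in changes of psychometric parameters of tinnitus (tinnitus minimal masking level and tinnitus loudness) as assessed by audiological evaluation (screening versus day 18". For cortical excitability it is "voxel-based morphometry (VBM) and paired-pulse TMS (baseline versus day 12". Table 1 confirms one pre-treatment and one post-treatment assessment for each.

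The same section analyses the primary endpoint, change in TQ score, differently: "in an analysis of covariance including treatment and average baseline score as fixed factors and center as a random factor". The sample size section reports that a simulation examined the effect of bringing centre and baseline into that analysis.

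Allocation is made "with a 1:1 treatment ratio, stratified by study center and with randomly varying block sizes", in 8 centres according to the Timing section. The Study treatments section names two makes of device and says that "stimulators will be used for stimulation as available in the participating centers". Nothing in the article adds a baseline covariate or a centre term to the one-way ANOVA.

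**The concern.** A one-way model has one factor, here treatment. With two arms, a one-way ANOVA of change is the unpaired t-test of change. It forces a coefficient of 1 on the pre-treatment value when ANCOVA would estimate that coefficient from the data. It also omits the factor on which randomisation was stratified.

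At stake is the width of the confidence intervals for minimal masking level, tinnitus loudness and paired-pulse TMS, together with the sensitivity of these estimates to whatever baseline difference randomisation happens to produce. The article names the method, so this is a choice already made and not a detail left to a later document. It gives no reason for dropping two terms that the primary model includes.

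**Working it through.** **Benchmark.** The article's only sample size is for TQ: effect size 0.486, two-sided α = 0.05, power 0.80, 68 per arm. The normal approximation gives 2 × (1.960 + 0.842)² / 0.486² = 66.5, so 67 per arm. The exact t-test gives 67.43, so 68 per arm, with power 0.803. The stated figure reproduces. No power target is given for the audiological or excitability outcomes; below, this figure serves only as a yardstick.

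**Variances.** Let s₀ and s₁ be the standard deviations before and after treatment and ρ their within-arm correlation.
- Change score: s₀² + s₁² − 2ρs₀s₁
- ANCOVA residual: s₁²(1 − ρ²)
- Difference: (s₀ − ρs₁)², which is never negative

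So in large samples ANCOVA is never the less precise. If s₀ = s₁ = s (an assumption), the change-score variance is 2s²(1−ρ), the ANCOVA variance is s²(1−ρ²), and their ratio is (1+ρ)/2.

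**Size over an assumed range of ρ.** The documents give no ρ for these measures. The third column is 138 divided by the ratio. The fourth supposes that the ANOVA of change has about 80% power at 68 per arm.

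| ρ (assumed) | Variance ratio | Patients needed by ANOVA of change to match ANCOVA on 138 | ANCOVA power | Shift of ANOVA estimate for a 0.2 SD baseline imbalance |
|---|---|---|---|---|
| 0.3 | 0.65 | 212 | about 94% | −0.14 SD |
| 0.5 | 0.75 | 184 | about 90% | −0.10 SD |
| 0.7 | 0.85 | 162 | about 86% | −0.06 SD |
| 0.9 | 0.95 | 145 | about 82% | −0.02 SD |

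**Chance imbalance.** With equal variances, the expected change-score estimate given a baseline difference D is the true effect minus (1−ρ)D, which gives the last column. With 69 per arm the standard error of D is √(2/69) = 0.17 SD, so a 0.2 SD imbalance is about 1.2 standard errors and would be unremarkable.

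**Simulation check.** The setting was 8 centres, 72 patients per arm, 1:1 within centre, 4000 runs per setting, with centre fitted as fixed effects and an assumed centre share of variance of 0 to 0.10.
- With no treatment or centre effect, the standard deviations of the two estimates were 0.168 and 0.146 at ρ = 0.5, 0.131 and 0.121 at 0.7, and 0.075 and 0.073 at 0.9. The squared ratios are 0.76, 0.85 and 0.95, in line with the formula.
- Averaged over randomisations, both estimates were unbiased.
- The slope of the ANOVA estimate on baseline imbalance was about −0.50, −0.30 and −0.10 at ρ = 0.5, 0.7 and 0.9. For the adjusted estimate it was about 0.
- Power for an effect of 0.486 SD of change, ANOVA against adjusted model, was 0.80–0.83 against 0.91 (ρ = 0.5), 0.80–0.83 against 0.88–0.89 (ρ = 0.7), and 0.79–0.83 against 0.84–0.85 (ρ = 0.9).
- With a centre share of 0.10, the ANOVA's type I error was about 0.038–0.042, which is mildly conservative.

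**The case against.** The strongest reply is that the planned test is sound. It is randomisation-valid, unbiased on average and at worst a little conservative; it concerns secondary outcomes, and the size of any gain rests on a correlation that nobody has stated. All of that stands, and it limits the point to precision. It does not favour the ANOVA, which uses the same data without gaining anything in large samples.

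Several stronger readings are tempting but unsupported:
- A reader might infer that the baseline is ignored. It is not: the outcome is a change, so the baseline is subtracted. It is only not a covariate.
- A reader might infer a biased comparison. The shift exists only conditionally on a chance imbalance and averages to zero over randomisations.
- A reader might infer that all between-centre variance stays in the error term, given the different stimulators. A stable centre offset is present before and after treatment and cancels. Only differences between centres in mean change remain, and the article gives no figure for them.
- A reader might see a contradiction with the primary analysis. The article assigns methods outcome by outcome and nothing requires one model for all. This is an unexplained difference, not a contradiction.
- A reader might treat these as the trial's only objective or mechanistic outcomes. Voxel-based morphometry is a secondary outcome too, and attentional testing and pure tone audiometry are recorded for safety.

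One point weighs the other way. The audiological pre-treatment value is a single result from routine screening, whereas TQ and THI baselines are averages of three. That makes a lower ρ plausible for audiology but does not establish it.

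**Conclusion.** The point holds as a recommendation on efficiency. For cortical excitability, minimal masking level and tinnitus loudness, the plan specifies an analysis that in large samples is never more precise than the form used for its own primary endpoint and is more exposed to chance baseline imbalance. Under equal variances, adjusting for the pre-treatment value lowers the variance by 35% at ρ = 0.3, 25% at 0.5, 15% at 0.7 and 5% at 0.9. The gain is material at low ρ and small near 0.9, and the documents do not show where these measures lie. The centre term may add little; omitting it makes the test at most mildly conservative and does not inflate false positives. The primary analysis, the sample size and the interim analysis are not affected.

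**What to change.** In the Statistical Analysis section, replace the one-way ANOVA for these outcomes with the primary model's form: treatment, the outcome's own pre-treatment value (screening for masking level and loudness, baseline for paired-pulse TMS), and centre as a random factor. Either the post-treatment value or the change can be the response; with the pre-treatment value in the model, the treatment estimate is the same. Report adjusted differences with 95% confidence intervals. The cost is one sentence of protocol or analysis-plan text, best settled before unblinding. No further data, visits or patients are needed.

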### Procedures

#### Visit schedule

An overview on the time schedule for assessing and recording of efficacy and safety parameters is given in table 1. Baseline assessments are followed by the two weeks treatment period, when the patient is seen daily from Monday to Friday (total of 10 visits). During the follow-up, patients will be seen at day 18 (visit 12), day 67 (visit 13) and at the final visit at day 181. In case of treatment discontinuation, efficacy parameters should be assessed for the whole study period at all outstanding visits (visits 6, 11–14, respectively). For patients who discontinue the study, the premature termination visit will be performed whenever possible.

**Table 1 T1:** Study Plan

	**Screening**	**Baseline**	**R**^3^	**Treatment**										**Follow-Up**		
Visits	V0	V1		V2	V3	V4	V5	V6	V7	V8	V9	V10	V11	V12	V13	final visit^4^

**Week**		Week 0		Week 1					Week 2					Week 3	Week 10	Week 26/PTV

**Day**		- 11 to -9		1	2	3	4	5	8	9	10	11	12	17 – 19	66–68	180 – 182
**Rating Scales (THI)**	X^1^	X^2^						X					X	X	X	X
**Otologic examination and audiological assessment**	X^1^													X		
**Informed Consent**	X															
**Demographic Data**	X															
**Medical History**	X															
**Documentation of Comorbidity**	X	X														
**Documentation of concomitant medication**	X	X											X	X	X	X
**Physical examination**		X											X			X
**Vital Signs**		X		X									X			X
**Rating Scales (Goebel&Hiller, BDI, SF 12)**		X^2^						X					X	X	X	X
**Tinnitus-Severity**		X		X				X					X	X	X	X
**NEO FFI, RS-11**		X														
**CGI**		X		X				X					X	X	X	X
**Neuropsychological Assessment**		X											X			
**Cortical Excitability (pTMS)**		X											X			
**Structural Neuroimaging (VBM)**		X											X			
**Inclusion/Exclusion**		X														
**Randomization**			X													
**rTMS Treatment**				X	X	X	X	X	X	X	X	X	X			
**Documentation of Adverse Events**				X	X	X	X	X	X	X	X	X	X			

^1 ^= results of routine clinical investigations

^2 ^= each patient receives at V1 two versions of THI and TQ to be completed on Monday and Friday before V2

^3 ^= randomisation

^4 ^= Visit 14 or PTV = Premature Termination Visit

#### Data collection

All randomized patients will receive a profound physical, neuropsychological and audiological examination at the screening and baseline visits, respectively. Beside a detailed physical examination, vital signs (e.g. heart rate, blood pressure, height and weight) will be determined at visits 2, 11 and 14. Neuropsychological parameters (test for attentional performance; TAP) will serve as a safety criterion to detect any deterioration in cognitive function and will be repeated at visit 11 (day 12) at the end of the treatment period. Audiological examinations at screening and visit 12 (day 18) will serve as both secondary outcome (tinnitus masking and loudness matching) and safety parameter (pure tone audiometry). Concomitant medication will be documented at screening and baseline, visit 11 at the end of the treatment period as well as at each follow-up visit. Tinnitus-specific rating scales (THI and TQ) will be performed three times during the baseline week before treatment and thereafter at visits 6 and 11 – 14 together with BDI and SF-12. Moreover, information on any adverse event, including side effects of study treatments, will be collected during the treatment period (visits 2 – 11). An independent data safety and monitor board (DSMB) consisting of clinical and statistical experts will critically assess adherence to the study protocol as well as to ICH-GCP-guidelines. Together with the sponsor, the DSMB will decide whether the trial has to be terminated prematurely. Possible reasons encompass e.g. safety concerns, unexpected high discontinuation rates or a large effect size on TQ at day 12 determined by the interim analysis.

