## Methods

### Design of the trial

This is a multicenter, randomized, patient and observer-blind, sham-controlled, parallel-group study of 2 weeks 1 Hz rTMS treatment plus 24 weeks follow-up in patients with moderate to severe chronic tinnitus. Eligible patients will be randomly assigned to either 2 weeks real rTMS treatment or sham treatment (figure 1).

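### Routine adverse-event documentation stops at visit 11 (day 12), so non-serious events after the last session and during the 24-week follow-up have no stated recording point

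*Protocol article*

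**What the plan says.** In the protocol article, the Data collection section says that "information on any adverse event, including side effects of study treatments, will be collected during the treatment period" and specifies visits 2 to 11 in brackets. The Visit schedule section introduces the study plan with the statement that "An overview on the time schedule for assessing and recording of efficacy and safety parameters is given in table 1". In that table the row "Documentation of Adverse Events" is marked at visits 2 to 11 and is blank at visits 12 and 13 and in the last column. Footnote 4 defines that last column as "Visit 14 or PTV = Premature Termination Visit", so the early-termination visit has the same blank cell as the scheduled final visit.

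Four other statements bear on the point:

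- Design of the trial gives the duration as "2 weeks 1 Hz rTMS treatment plus 24 weeks follow-up".
- Data collection says "Audiological examinations at screening and visit 12 (day 18) will serve as both secondary outcome" and goes on to name pure tone audiometry as the safety component.
- Concomitant medication is documented at visit 11 and at every follow-up visit.
- For patients who discontinue treatment, Visit schedule says that "efficacy parameters should be assessed for the whole study period at all outstanding visits".

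**The concern.** Benefit is followed to week 26, while harm, as routinely documented, is followed only to the last treatment day. The article's own Safety of rTMS section lists headache following stimulation as an expected side effect. After each of the first nine sessions there is another treatment visit at which such a headache can be noted. After the tenth there is none.

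In follow-up, the case report form would show a newly started drug but has no scheduled entry for the event that prompted it. A patient who stops attending because of something that happened after a session may come to a premature termination visit, and the schedule has no adverse-event entry there either. At stake is the completeness of the comparison of non-serious events between real and sham stimulation. Events not asked about at the time are hard to reconstruct later.

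**Working it through.** **Is the window stated or inferred?** It is stated twice and consistently. The text gives visits 2 to 11. Table 1 has ten adverse-event marks, at visits 2 to 11 (days 1 to 12). Because Table 1 is presented as the schedule for safety as well as efficacy recording, the blank cells are a rule and not detail left out of a condensed article.

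**What is covered and what is not** (days from Table 1 and Visit schedule):

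- Treatment visits covered: 10 of 10.
- Visits from visit 2 to visit 14: 13. Covered: 10. Not covered: 13 − 10 = 3 (visits 12, 13 and 14/premature termination).
- Time after the window closes: 181 − 12 = 169 days, and 169 / 7 = 24.1 weeks, which matches the stated 24-week follow-up.
- Safety audiogram: day 17 to 19, so 17 − 12 = 5 to 19 − 12 = 7 days after the window closes.
- Calendar share covered: 12 / 181 = 6.6%. This counts days, not exposure, and is not a measure of how many events are missed.

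**What is collected at the three uncovered visits** (Table 1):

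- Visit 12: tinnitus questionnaires, tinnitus severity, BDI, SF 12, CGI, concomitant medication, otologic and audiological assessment.
- Visit 13: the same scales and concomitant medication.
- Final or premature termination visit: the same scales, concomitant medication, physical examination, vital signs.

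None has an adverse-event entry, so an event such as headache could appear only indirectly, for example through a drug taken for it.

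**Rough size of the tenth-session gap.** Safety of rTMS gives an incidence of about 5% and does not say whether this is per session or per patient. With 150 randomised 1:1, the real arm has 150 / 2 = 75 patients.

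- If 5% is per patient over the course and spread evenly over ten sessions: 75 × 0.05 / 10 ≈ 0.4 patients with headache after session ten.
- If 5% is per session: 75 × 0.05 = 3.75 patients.

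Both figures assume that all 75 receive the tenth session. Both are upper limits for what is lost, since a headache that starts before the patient leaves visit 11 can still be recorded there. The document gives no event rate for follow-up, so that part of the gap cannot be sized.

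**After the fix:** 10 + 3 = 13 of 13 visits from visit 2 onward would have adverse-event documentation.

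**The case against.** The strongest reply is that the window fits the exposure. All ten treatment days are covered, the expected effects are short-lived, and only one session of ten lacks a later visit, in both arms alike. That holds as an argument about size. It does not give later non-serious events a place to be recorded.

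Several stronger readings are tempting, and the document does not support them:

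- *Worsening tinnitus or hearing goes unrecorded after day 12.* It does not. Both tinnitus questionnaires, tinnitus severity and CGI are scheduled at every follow-up visit, and the visit 12 audiogram is itself safety data that can be compared with screening.
- *Patients who stop treatment are followed for efficacy only.* The text requires efficacy assessments at the outstanding visits. It does not say only, and it does not exclude safety recording.
- *Anyone who stops because of an event goes unrecorded.* An event noted at an attended treatment visit falls inside the window. The gap concerns events after the last attended treatment visit.
- *The baseline paired-pulse TMS leaves a gap that biases the comparison.* That procedure precedes randomisation, so its events cannot bear on real versus sham, and one that persisted could be noted at visit 2.
- *Serious events in follow-up go unreported.* Rules for serious events are commonly left to the full protocol, which is not shown, and the article commits to ICH-GCP.
- *The DSMB would see truncated data.* The article does not say which data the board receives.

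**Conclusion.** The point holds in a limited form. The schedule provides no routine adverse-event documentation at visit 12, visit 13 or the final or premature termination visit. This leaves without a stated recording point those non-serious events that arise after the tenth session, during the 169 days of follow-up, or after the last treatment visit attended by a patient who leaves early. The gap is 3 of 13 visits from visit 2 onward, with complete coverage on treatment days.

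The conclusion rests on the published text and Table 1. It assumes that the full protocol does not schedule routine recording at later visits, which would contradict both. The consequence is a less complete safety comparison. Efficacy, power and type I error are untouched, and a reader should not infer that the trial fails to monitor safety. This is a worthwhile, low-cost improvement and not a must-fix.

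**What to change.** In Table 1 and the Data collection section, extend the adverse-event row to visit 12, visit 13 and the final or premature termination visit, and state that this applies equally to patients who have discontinued treatment. Say also that the change in pure tone audiometry from screening to visit 12 will be reported by arm with the safety results. There is no need to class every threshold shift as an adverse event: without a minimum shift, ordinary measurement variation would count.

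The cost is one case report form entry and a few minutes at each of three visits that already take place. Sample size, interim and final significance levels and the primary analysis stay as they are.
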